#### Intervention adherence

Throughout the trial, lenalidomide and ixazomib will be taken orally and swallowed whole at the same time on the scheduled days. Dexamethasone will be administrated in accordance with the relevant Summary of Product Characteristics (SPCs). To monitor treatment adherence, participants will complete a daily medication diary, which will be reviewed at trial visits. Unused capsules will be returned to pharmacy.

#### Dose modification and discontinuation

Both R1 and R2 treatment cycles will be 28 days in length. Response will be assessed at the end of each cycle according to the IMWG 2016 Uniform Response Criteria.^26 27^ In the absence of progression or treatment intolerance, participants will receive a maximum of 12 cycles of induction therapy and continuous maintenance therapy. Those who receive 12 cycles of induction therapy will be assessed for R2 eligibility, with non-eligible participants being treated off trial.

Toxicity and hence treatment intolerance will be assessed throughout each treatment cycle, according to the National Cancer Institute (NCI) common terminology criteria for AE (CTCAE) V.5.

For a new cycle of treatment to begin (induction and maintenance), the participant must meet the haematological and biochemical criteria (at day 1 or ≤3 days prior) outlined in the eligibility criteria (R1: box 1, R2: box 2). Non-haematological toxicities (except for alopecia) must have resolved to less than or equal to grade 1 or to the participants’ baseline condition in order for treatment to resume. If the participant does not meet these criteria, their dose will be delayed for 1 week before they are reassessed. This will continue for a maximum of 3 weeks before treatment discontinuation or 8 weeks at the discretion of the chief investigator.

In the event that a dose is reduced due to toxicity, as per the lenalidomide SPC the dose may be reintroduced to the next higher dose level on improvement. Ixazomib, once reduced cannot be re-escalated.

#### Concomitant medication

Concomitant medication, disease and other malignancies will be recorded at eligibility.

All participants may receive additional care during the treatment period as deemed appropriate by the treating clinician. Local support care protocols, including antiemetic schedules, tumour lysis syndrome prevention, venous thromboembolism prophylaxis and prophylactic antimicrobial therapy, will be followed for both randomisations. Permitted and excluded concomitant medications and procedures can be found in the online supplemental material.

### Outcomes

#### Primary outcome

For R1, the primary outcome is early treatment cessation (defined as a binary endpoint) for reactive versus adaptive dosing in participants defined to be ‘unfit’ or ‘frail’ at baseline. Participants will be defined to have experienced an event if they die, progress, or are withdrawn from treatment (by the treating clinician) or withdraw consent for treatment, within 60 days of R1.

For R2, the primary outcome is PFS for R+placebo versus R+I, and is defined as the time from R2 to the time of first documented disease progression or death from any cause. Individuals lost to follow-up or progression free at time of analysis will be censored at their last known alive and progression-free date.

#### Secondary outcomes

The secondary outcomes of this trial are to assess PFS for reactive versus adaptive dosing, time to progression, time to 2nd PFS event, OS, survival after progression, deaths within 12 months of R1, overall response rate, attainment of ≥ very good partial response (VGPR), attainment of minimal residual disease (MRD) negativity (flow MRD will be assessed only. Additional detail on the testing of MRD and timepoints is presented in the ‘central lab analysis’ section of the online supplemental material), duration of response, time to improved response, time to next treatment, treatment compliance and total amount of therapy delivered, toxicity and safety including the incidence of second primary malignancies, quality of life (QoL), cost-effectiveness of reactive versus adaptive dosing of IRD and cost-effectiveness of R+I versus R.

#### Exploratory outcomes

Exploratory outcomes are to prospectively validate the UK Myeloma Research Alliance (UK-MRA) Myeloma Risk Profile, to assess the usefulness of the Karnofsky performance status, and consider the association of molecular subgroups with response, PFS and OS.

### Participants timelines

The full trial schema can be seen in figure 3. The schedule of assessments at each timepoint is presented in figure 4.

**Figure 3 F3:**
[figure not shown]
Flow diagram of Myeloma XIV (Frailty-adjusted therapy in Transplant Non-Eligible patients with newly diagnosed Multiple Myeloma) Trial. ADL, activity of daily living; HE, health economics; IADL, instrumental activity of daily living; IMWG, International Myeloma Working Group; IRD, ixazomib, lenalidomide and dexamethasone; QoL, quality of life; R+I, lenalidomide+ixazomib.

**Figure 4 F4:**
[figure not shown]
Summary of investigations (local and central). ADL, activity of daily living; ALT, alanine aminotransferase; AST, aspartate aminotransferase; BP, blood pressure; CR, complete response; CRP, C-reactive protein; CTRU, Clinical Trial Research Unit; eCRFs, electronic case report forms; EDTA, edetic acid; EORTC QLQ C30, European Organisation for Research and Treatment of cancer quality of life questionaire; EQ-5D, Euroqol 5 dimensions; FBC, full blood count; FISH, fluorescence in situ hybridization; HMDS, Haematology Malignancy Diagnostic Service; IADL, instrumental activity of daily living; ICR, Institute of Cancer Research; IMWG, International Myeloma Working Group; IRD, ixazomib, lenalidomide and dexamethasone; LDH, lactate dehydrogenase; LFTs, liver function test; LIMR, Leeds Institute of Medical Research; MRD, minimal residual disease; QLQ-MY20, myeloma quality of life questionaire; SAEs, serious adverse events; sCR, stringent complete response; SPMs, secondary primary malignancies; SUSARs, suspected unexpected serious adverse reactions; U&E's, urea and electrolytes. a. The FBC should be repeated mid-cycle 1 (Day 14 +/−3 days) or more frequently and during subsequent cycles if there is a concern about cytopenias, b. Pregnancy test must also be performed at 4 weeks after the end of study treatment, c. Or at 6 and 12 months post-R2 if treatment is stopped prior to this for reasons other than disease progression, d. Or at 2, 6 and 12 months post-R1 if treatment is stopped prior to this for reasons other than disease progression, e. The imaging at baseline/pre-registration is mandatory. Subsequent imaging will be as per local protocols/standard of care - imaging will only need to be repeated if extramedullary disease was detected at baseline, or in the event of new symptoms suggestive of new extramedullary disease, cord compression, new fracture, etc, or to investigate new hypercalcaemia. In the rare event of participants with extramedullary disease at baseline, imaging should be performed at the end of IRD induction to confirm the end of induction response, and at any other time the disease parameters suggest that the participant has achieved a complete response (if not already achieved at the end of induction) to confirm that the extramedullary disease has resolved, f. Performance status should be recorded at the same timepoints as the frailty index (ie, prior to R1, after cycles 2, 4, 6 and 12 of induction, and after cycles 6 and 12 of maintenance). Performance status should also be recorded at the time of disease progression. Or at 2, 6 and 12 months post-R1 if treatment is stopped prior to this for reasons other than disease progression, g. If the participant did not consent to the pre-trial bone marrow registration part of Myeloma XIV, the bone marrow biopsy will need to be taken after full informed consent. ^¥^If not sent at bone marrow and blood sample consent, *At pre-randomisation 1 a CD138 negative portion of the bone marrow aspirate will be sent to LIMR after CD138 positive selection at ICR, **At the end of induction bone marrow aspirate will be sent to ICR after CD138 positive selection at LIMR.

#### Trial entry

Participants will enter the trial at one of two points in their patient pathway, this will either at bone marrow registration or main trial registration.

#### Trial consent

Participants who enter the trial at bone marrow registration will provide consent to having bone marrow and blood samples taken and sent to central laboratories for analysis. If the participant is diagnosed with a plasma cell dyscrasia, other than myeloma, or they have myeloma, but decide not to take part in the FiTNEss trial, they will also have the option of consenting to their samples being used in future research.

All participants will provide written informed consent for the trial prior to trial registration. Optional consent for QoL resources and the use of samples for future research will also be obtained.

#### Trial registration

Following trial consent, participants will be registered onto the main trial and assessed for eligibility. Consenting patients will complete the baseline QoL and healthcare resource use questionnaires. Trial samples for blood and urine will be taken for all participants, and bone marrow samples will be taken for those who did not enter the trial through bone marrow registration.

#### Trial treatment

Following trial registration, participants will be randomised into R1 and treated as described in the intervention schedule on a monthly basis. In absence of disease progression or intolerance, those participants with at least an MR following 12 cycles of maintenance and whom meet all of the R2 eligibility criteria will proceed to R2 maintenance treatment.

Participants will be followed up monthly (at each cycle) while receiving maintenance treatment, until death or until the final analysis of the trial (whichever happens sooner).

#### Trial follow-up

Participants who discontinue treatment during induction and before the point of R2 will be followed up to the point of assessment for eligibility for R2, unless they withdraw consent for this. Thereafter, participants will continue to be followed-up for data pertaining to safety, progression (including second progression), and survival. Frailty scores will be completed for all participants at 2, 4, 6 and 12 months post R1, irrespective of whether they have discontinued treatment. Similarly, QoL and healthcare resources use questionnaires (if the participant has consented to these) will continue to be completed at 2, 6 and 12 months post R1.

If treatment has been stopped without progression following R2, for example, due to toxicity, then participants will be followed up 2 monthly until disease progression. Follow-up will include local investigations, central investigations, frailty index at 6 and 12 months post R2 and QoL and healthcare resource use at 6 and 12 months post R2 (if consented).

### Sample size

In total, 740 participants will be enrolled into the trial at R1 to ensure that at least 478 participants remain on trial and are randomised to R2. It is assumed that 65% of those randomised at R1 will be progression free and, therefore, eligible for R2, hence 740 participants are required to be enrolled.

Based on data from the Myeloma XI non-intensive pathway, we hypothesise the frail and unfit patients in R1 will be similar to the older patients in Myeloma XI (>75 years) who have an early treatment cessation rate (within 60 days of R1) of 20%. This hypothesis is based on the expectation that the frailty score is heavily driven by patient age. Younger patients (≤75 years) in the Myeloma XI non-intensive pathway have an early treatment cessation rate of 9%, and it is our hypothesis that our frailty-based dosing schedule has the potential to reduce the rate among the unfit and frail patients to the proportion observed in fit patients.^28 29^

To demonstrate a decrease of 11% in the proportion of early treatment cessation from 20% in the standard dosing schedule arm to 9% in the frailty score-adjusted dose arm among those patients scored at baseline to be unfit or frail would require the recruitment of 324 patients with an allocation ratio of 1:1. These calculations are based on a Pearson’s χ^2^ test without continuity correction, assume a two-sided 5% level of significance, 80% power, and allow for a 1% dropout prior to 60 days post randomisation. Given that we anticipate that 45% of patients will be scored as unfit or frail, by assuming this trial will have a similar underlying population as in Myeloma XI non-intensive pathway and the age distributions in the IMWG report proposing the frailty score,^14^ we would anticipate that we will require 720 patients to enter the trial at R1 to have sufficient unfit and frail patients available to answer this question.

For R2, in the non-intensive pathway of Myeloma XI, the median PFS for patients on R following CRDa induction was approximately 33 months,^19^ where approximately 65% of individuals were progression-free 12 months post randomisation. As R2 is approximately 12 months following R1 in FiTNEss, we assume that the median PFS for patients receiving R maintenance therapy will be 21 months from R2. Tourmaline-MM1^12^ demonstrated an HR for PFS of 0.74 when comparing IRD and RD in patients with relapsed and refractory multiple myeloma. Thus a similar HR would be the minimum clinically relevant difference for our comparison in patients with newly diagnosed multiple myeloma. Assuming a median PFS of 29 months for those in the R+I maintenance group in addition to the assumption of 21 months in the R group equates to an HR of 0.72.

The above assumptions require the recruitment of 478 participants over a 30 month recruitment period with a further 24 months of follow-up. These calculations also assume a two-sided 5% significance level, 80% power and allow for a 3% dropout rate prior to a PFS event being experienced. Note that 80% power is attained when 302 events have been observed. A total of 740 participants should be allocated to R1 to ensure that 478 participants are available at the second randomisation.

OS is considered to be a key secondary endpoint for R2, 180 events with a minimum of 2-year follow-up for all participants are required for 80% power.

### Recruitment

It is planned that 740 participants will be recruited over a 30-month recruitment period from 87 UK centres. Once all centres are open, the recruitment target is 30 participants a month. The trial opened to recruitment on 4 August 2020. As of May 2021, 85 sites are open to recruitment and 137 participants have been randomised to the first stage of the trial.

In order to ensure the trial will meet the target sample size within the recruitment period, site set-up was prioritised while the trial was preparing to open to recruitment. In addition, the trial team are actively engaging with principal investigators at sites who support the trial to ensure that those sites open quickly and are maintaining regular communication with open sites to ensure that they continue to recruit to the trial. Finally, while the trial was originally delayed due to the COVID-19 pandemic, efforts were made to ensure that it opened as soon as possible when research restarted. One factor being the positive risk to benefit ratio of the number of hospital visits required for the trial interventions as compared with standard of care.

### Assignment of treatment allocations

Each of the registration and randomisation procedures will be conducted centrally using the Leeds Clinical Trial Research Unit (CTRU) automated 24-hour web-based and telephone system.

### Registrations

If a patient is suspected to have myeloma, they will enter the trial at the time of routine diagnostic tests, through bone marrow registration. Once diagnosis is confirmed locally and the research team consider the patient potentially eligible for the trial, patients will be provided with full verbal explanation of the trial and the full participant information sheet and informed consent documents to consider. Once the participant has provided informed consent, they will be registered onto the trial.

Other participants who have myeloma confirmed prior to entering trial will enter at trial registration.

### Randomisations

Following trial registration, patients will be assessed for R1 eligibility. Eligible participants will be randomised on a 1:1 basis into R1, using the stratification factors; centre, IMWG frailty category, beta-2 microglobulin concentration (<3.5, 3.5 to <5.5, ≥5.5 mg/L), Haemaglobulin concentration (<100, ≥100 g/L, serum crestinine concentration (<175, ≥175 µmol/L), corrected serum calcium concentration (<2.75, ≥2.75 mmol/L) and platelets (<150, ≥150×10^9^/L).

Following R1, and as soon as the end of induction response is known, R2 eligible participants will be randomised on a 1:1 basis into R2, using the stratification factors; centre, allocated induction arm (reactive, adaptive); final response to induction treatment (<VGPR, ≥ VGPR).

For both R1 and R2, a computer generated minimization programme that incorporates a random element will be used to ensure treatment groups are well balanced for the specified stratification factors.

### Blinding methods

For R2 treatment, allocation will be concealed from participants, treatment provider and the trial team. The placebo and ixazomib capsules will be identical in colour, size, packaging and labelling.

To maintain the overall integrity of the trial design, unblinding will only be permitted in exceptional circumstances; for example, valid medical or safety reasons where assuming that the patient is receiving active treatment and/or stopping the blinded medication is insufficient.

Unblinding will be conducted automatically using an online system accessed by an authorised member of the site research team.

If unblinding is performed at any stage during the trial, decisions around further trial treatment will be the responsibility of the principal investigator or delegate. In either case, unblinded participants will be followed up as per the protocol.

At the completion of the trial and after final analysis, participants will be given the opportunity to be informed of their allocation by their research site.

### Data collection

Clinical data will be collected both electronically and on paper by staff at the research site completing CRFs provided by CTRU. QoL and Healthcare Resource Use questionnaires will be completed on paper CRFs by the participant. All paper CRFs will be sent to CTRU, by the research site, usually via standard post and entered onto an electronic database. These data along with the data entered electronically by staff at each research sites will be validated and monitored for completeness and quality by the CTRU.

Missing data will be chased until it is received, confirmed as not available or the trial is at analysis. Missing QoL data items will not be chased from participants, although missing questionnaires may be chased from sites.

### Data management

Validation checks will be incorporated into the trial database to verify the data, and discrepancy reports will be generated for resolution by the trial site. Priority validations will be incorporated to ensure that any discrepancies related to participant rights, or the safety of participants, are expedited to sites for resolution. The CTRU/Sponsor will reserve the right to intermittently conduct source data verification exercises on a sample of participants, which will be carried out by staff from the CTRU/Sponsor. Source data verification will involve direct access to participant notes at the participating hospital sites and the ongoing central collection of copies of consent forms and other relevant investigation reports.

### Statistical methods

Statistical analysis is the responsibility of the CTRU statisticians, with the exception of the analysis for cost-effectiveness of delivery of IRD and R/R+I, which will be undertaken by Health Economists at the University of Leeds. A full statistical analysis plan and health economics analysis plan (HEAP) will be written and approved before any analysis is undertaken.

All analyses will be conducted on the intention-to-treat population, where participants will be included according to their randomisation allocation regardless of eligibility, whether they prematurely discontinued treatment, or did not comply with the regimen. A per-protocol analysis, where participants will be included if they received their allocated intervention according to the protocol, will be considered for the primary endpoints if there are a considerable number of major protocol violators. The safety population will consist of all participants who received at least one dose of the trial treatment and participants will be summarised as per their treatment received rather than their allocation.

An overall two-sided 5% significance level will be used for all efficacy endpoint comparisons. For the primary endpoints, this will be adjusted to account for the formal interim analyses.

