#### Primary endpoint analysis

##### Randomisation 1

For R1, the number and proportion of participants, categorised as unfit or frail at baseline, experiencing an early treatment cessation event will be summarised by randomisation allocation and exact 95% CIs will be calculated.

A logistic regression model will regress early treatment cessation on randomisation allocation (reactive/adaptive dosing) adjusting for the stratification factors of the trial. A statistically significant induction treatment effect will be suggested if the p value for the resulting OR is <0.047. Parameter estimates, ORs and corresponding 95% CIs, df, test statistics and p values will be presented for each variable in the model. Residuals and predicted values produced from the models will be examined to assess the assumptions of the statistical models.

##### Randomisation 2

For R2, PFS between the two maintenance therapies (R+placebo/R+I) will be compared using a Cox regression model adjusting for the stratification factors of the trial. A statistically significant maintenance treatment effect will be suggested if the p value for the HR corresponding to randomisation allocation is <0.047. Parameter estimates, HRs and corresponding 95% CIs, df, test statistics and p values will be presented for each variable in the model.

The proportional hazards assumptions will be assessed by plotting the hazards over time (ie, the log cumulative hazard plot) for each treatment arm and using appropriate statistical tests. If evidence is found to support the violation of the proportional hazards assumption, then alternative appropriate analysis methods will be investigated.

No imputation strategy is planned for the primary endpoints.

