#### Secondary endpoint analysis

Secondary endpoint analysis of OS and other time-to-event endpoints will be analysed using similar methods to those described for PFS.

MRD negativity and other binary endpoints will be analysed using similar methods to those described for the early treatment cessation primary endpoint. The number and proportion of participants in each response category (stringent complete response (sCR), complete response (CR), VGPR, etc) will be summarised by allocated treatment and exact 95% CIs will be calculated. The difference in proportions for each response category will be presented with corresponding 95% CIs.

The domains of the QoL questionnaires will be summarised using mean scores adjusted for baseline and 95% CIs at each assessment timepoint. Similar summaries will be produced for quality-adjusted life years (QALYs) derived using the EQ-5D-3L (Euroqol 5 dimensions) questionnaire.

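### The flat two-sided 5% for all efficacy comparisons leaves the powered key secondary, overall survival at R2, testable whatever the R2 PFS result, and does not mark the other secondaries as supportive

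*Protocol article*

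**What the plan says.** Statistical methods sets one level for everything: "An overall two-sided 5% significance level will be used for all efficacy endpoint comparisons". The next sentence gives the only adjustment: "For the primary endpoints, this will be adjusted to account for the formal interim analyses". The resulting final threshold appears under Primary endpoint analysis, for example for R1: "A statistically significant induction treatment effect will be suggested if the p value for the resulting OR is <0.047". The same 0.047 is set for the R2 hazard ratio.

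Under Sample size, OS is set apart from the other secondaries: "OS is considered to be a key secondary endpoint for R2, 180 events with a minimum of 2-year follow-up for all participants are required for". The power named there is 80%. No hazard ratio or significance level is given for that calculation.

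Secondary outcomes lists, among others, "PFS for reactive versus adaptive dosing, time to progression, time to 2nd PFS event, OS, survival after progression, deaths within 12 months of R1", followed by response, MRD, duration-of-response and time-to-next-treatment endpoints. It does not say which endpoint belongs to which randomisation. Under Secondary endpoint analysis, "Secondary endpoint analysis of OS and other time-to-event endpoints will be analysed using similar methods to those described for PFS", and "MRD negativity and other binary endpoints will be analysed using similar methods to those described for the early treatment cessation primary endpoint". Quality of life is only summarised with means and confidence intervals. Exploratory outcomes are listed separately. A full statistical analysis plan is promised before any analysis.

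**The concern.** The text states a rule for the secondaries. It deals with repeated looks at the primaries and then gives every other efficacy comparison an unadjusted 5%.

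This matters most for R2 OS. An event target and a power figure are what one sets for a formal test. Followed literally, R2 could miss PFS at 0.047 and OS could still be tested at 0.05 and reported as positive. The trial would then have two routes to a positive maintenance claim, and the word overall in the 5% statement would not hold for the pair. A significant OS result would also be hard to present as confirmatory, although events were planned for it.

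The remaining secondaries are less critical, but nothing says that their p values are supportive. A reader of the results could not tell a planned claim from one low p value among ten or twelve.

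**Working it through.** **Inputs from the protocol article.** Two-sided 5% for all efficacy comparisons (Statistical methods); 0.047 as the final primary threshold (Primary endpoint analysis); medians of 21 and 29 months, 302 PFS events and 180 OS events, each for 80% power (Sample size); the list under Secondary outcomes.

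**Assumptions.** Endpoint counts: 12 efficacy-type secondaries for R1 (PFS, time to progression, time to second PFS event, OS, survival after progression, deaths within 12 months of R1, overall response, at least VGPR, MRD negativity, duration of response, time to improved response, time to next treatment). For R2, remove PFS (primary there) and deaths within 12 months of R1, which leaves 10, OS included. Quality of life is not counted because no test is stated. Correlation ρ between test statistics: 0 to 0.8, equal for all pairs.

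**1. Reproduce the plan's own figure.** Schoenfeld events for R2 PFS: 4(1.960 + 0.842)² / [ln(21/29)]² = 4 × 7.849 / 0.1042 = 301.4, rounded up to 302. This matches, so the design is a single two-sided 5% test of PFS.

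**2. What the 180 OS events imply.** Solving the same formula for the hazard ratio at two-sided 5% and 80% power: exp(−2.802/√(180/4)) = exp(−2.802/6.708) = 0.659. This value is back-solved, since the article states none. It shows that the target corresponds to OS tested at the full 5% if the true hazard ratio is about 0.66.

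**3. R2 PFS and OS as a pair.** With neither effect present and each tested at 5%, the chance of at least one rejection at ρ = 0 is 1 − 0.95² = 0.0975. For ρ > 0 it is 1 − P(both |Z| ≤ 1.96) for correlated normal statistics:

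| ρ | 0 | 0.3 | 0.5 | 0.8 |
|---|---|---|---|---|
| PFS and OS each at 0.05 | 0.098 | 0.095 | 0.091 | 0.078 |
| PFS at 0.047, OS at 0.05 | 0.095 | 0.092 | 0.088 | 0.076 |

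The first row is the better guide, because 0.047 is only the final-look threshold and PFS spends 5% over both looks.

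**4. The secondary list within each randomisation.** With no true effect on any endpoint and each test at 5%, the chance of at least one p<0.05 at ρ = 0 is 1 − 0.95^k. For k = 12 that is 0.460, and for k = 10 it is 0.401. With correlation:

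| ρ | 0 | 0.3 | 0.5 | 0.8 |
|---|---|---|---|---|
| R1, k = 12 | 0.460 | 0.397 | 0.319 | 0.186 |
| R2, k = 10 | 0.401 | 0.351 | 0.287 | 0.17 |

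Taking OS out of the R2 list (k = 9) gives 1 − 0.95⁹ = 0.370 at ρ = 0, so the picture does not depend on it.

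**5. Cost of the remedy in OS power.** If OS is tested at two-sided 5% only after R2 PFS succeeds, the level for OS is unchanged. At that test the 180 events still give 80% power at the hazard ratio of 0.66. A Bonferroni split over ten endpoints (0.05/10 = 0.005) would cut OS power to 49.8%.

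**The case against.** Four arguments on the other side deserve weight.

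- **The analysis plan may settle it.** Testing order is commonly left to the statistical analysis plan, and this is a condensed article. That would answer a complaint about silence. Here the article states a level for all efficacy comparisons, so a later hierarchy would have to narrow that sentence. The wording is therefore a fair target, although the plan may already contain the answer.
- **A ranking exists.** Endpoints are graded as primary, key secondary, secondary and exploratory, and secondary endpoints are by convention supportive. This stands. What is absent is narrower: a stated relation between R2 OS and R2 PFS, and a supportive label for the rest.
- **The decision rule is written only for the primaries.** The rule for calling an effect significant appears for the two primary tests, with a threshold specific to them. The secondary section borrows the models and states no decision rule. This also stands. That the trial would in fact announce a secondary benefit after a failed primary is an inference from the 5% sentence.
- **Nominal 5% testing of secondaries is common in academic phase III trials.** That is a reason to ask for a label on those results, without demanding formal control over all of them.

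A reader might go further and infer that at least one false secondary claim is likely. The documents do not support that. Within one randomisation the figure stays below 50% even with independent tests. These endpoints overlap heavily, so independence is unrealistic. Every figure also assumes no true effect on any endpoint. Pooling the two randomisations would raise the number, but R1 and R2 ask separate questions and the article does not treat them as one family.

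**Conclusion.** The point holds in a narrow form. The flat 5% rule leaves R2 OS, the one secondary with its own event target and power, testable at full level whether or not R2 PFS succeeds. The chance of a false claim on that pair is then about 8% to 10%, given no effect on either and a correlation between 0.8 and 0. This result needs no endpoint count.

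For the wider list, about 19% to 46% at R1 and 17% to 40% at R2 are the chances of at least one nominal p<0.05 under the global null. They rest on the assumed split of 12 and 10 endpoints and on equal correlations. They illustrate why a supportive label is needed and do not predict what this trial will report.

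Neither primary conclusion nor the sample size is affected. This is a cheap improvement to the wording; it does not reveal a flaw in the design.

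**What to change.** Replace the sentence in Statistical methods with three statements, and carry them into the statistical analysis plan:

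1. The two-sided 5% level applies to the primary endpoint of each randomisation, adjusted for its interim analysis as already planned.
2. R2 OS is tested confirmatorily at two-sided 5%, at 180 deaths and with the stated two-year minimum follow-up, only if R2 PFS is significant.
3. All other secondary comparisons at R1 and R2 are reported as estimates with 95% confidence intervals and nominal p values, labelled supportive.

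Gating on PFS is not the only valid choice; a separate level for OS, or labelling OS supportive as well, would also remove the ambiguity. Gating has the advantage of keeping OS at 5%, so the 180-event target needs no change.

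The cost is one paragraph, with no extra patients, visits or data. The downside is that OS is confirmatory only if PFS is positive, and the other secondaries support no confirmatory claim.
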